**Methods:**

The NEOCLOT study is a multicentre prospective observational cohort study, including 150 preterm and term infants (0-6 months) admitted to one of the 10 NICUs, developing CVC-thrombosis. Patient characteristics, thrombosis characteristics, risk factors, treatment strategies and outcome measures will be collected in a web-based database. Management of CVC-thrombosis will be performed as recommended in the protocol. Violations of the protocol will be noted. Primary outcome measures are a composite efficacy outcome consisting of death due to CVC-thrombosis and recurrent thrombosis, and a safety outcome consisting of the incidence of major bleedings during therapy. Secondary outcomes include individual components of primary efficacy outcome, clinically relevant non-major and minor bleedings and the frequency of risk factors, protocol variations, residual thrombosis and post thrombotic syndrome.

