### Study population

#### Inclusion criteria

All preterm and term infants (0-6 months) admitted on one of the NICUs with CVC-thrombosis will be included.

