#### CVC-thrombosis in a blood vein

Figure 1 shows the consensus-based algorithm regarding the proposed policy to CVC-thrombosis in a blood vein. High-risk CVC-thrombosis should be treated with thrombolytic therapy followed by anticoagulant therapy for at least 4 to 6 weeks. During thrombolysis ultrasonography will be performed once daily (see Table 1).

**Table 1 Tab1:** Thrombolytic therapy

Thrombolytic agent	Therapeutic dose	Monitoring
r-TPA	Start: 0.1 mg/kg/h iv Continuous infusion for longer periods with increasing doses if no improvement Max. dose: 0.5 mg/kg/h iv	Check CBC, APTT, PT, fibrinogen, D-dimers daily Exclude ICH by US daily Transfuse with FFP daily Maintain fibrinogen > 1.0 g/L and platelets > 50 × 10^9^/L Check thrombus resolution once to twice daily

*Abbreviations*: *r-TPA* recombinant tissue plasminogen activator, *h* hour, *iv* intravenously, *CBC* complete blood count, *APTT* activated partial thromboplastin time, *PT* prothrombin time, *ICH* intracranial hemorrhage, *US* ultrasound, *FFP* Fresh frozen plasma, *max* maximum

After cessation of thrombolysis, LMWH should always be started. After 4 to 6 weeks, ultrasonography will be performed. If the clot has disappeared, anticoagulation will be stopped.

For non-obstructive CVC-thrombosis, a “wait and see” policy is recommended, with Doppler ultrasonography follow-up within 5 days, depending on the size of thrombosis. If the size of thrombosis increases, anticoagulant therapy should be started. In all neonates with obstructive CVC-thrombosis and without indication for thrombolysis, anticoagulant therapy (LMWH) should be started immediately.

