### Outcome measures

#### Outcomes of primary aims

The primary efficacy outcome for the NEOCLOT study is a composite outcome consisting of recurrent thrombosis and death due to CVC-thrombosis after start of management of CVC-thrombosis. The primary safety outcome is the incidence of major bleedings during thrombolytic and anticoagulant therapy.

Major bleeding is defined as reported by Mitchell et al.: 1) fatal bleeding, 2) clinically overt bleeding associated with a decrease in hemoglobin of at least 20 g/L (i.e., 2 g/dL or 1.24 mmol/L) in a 24-h period, (3) bleeding that is retroperitoneal or pulmonary, or (4) bleeding that requires surgical intervention in an operating room [20]. Intracranial bleeding is categorized major bleeding as defined by Curley et al. in the Planet-2 study: Intraventricular haemorrhage (IVH) (H1, H2 or H3) with ventricular dilatation, IVH (H1, H2, H3) with parenchymal extension, any evolution of intracranial haemorrhage from IVH or germinal layer heamorrhage to IVH with ventricular dilatation or IVH with parenchymal extension [21].

The secondary efficacy outcomes are the individual components of the primary outcome, i.e. death due to CVC-thrombosis and recurrent thrombosis and all-cause mortality. The secondary safety outcomes include clinically relevant non-major bleeding (CRNMB) and minor bleedings during fibrinolytic and anticoagulant therapy as defined by Mitchell et al. [20]. All intracranial bleedings which are not defined as major bleeding will be categorized as non-major intracranial bleeding. CRNMB is a composite of (1) overt bleeding for which a blood product is administered and not directly attributable to the patient’s underlying medical condition and (2) bleeding that requires medical or surgical intervention to restore hemostasis, other than in an operating room. Minor bleeding is defined as any overt or macroscopic evidence of bleeding that does not fulfil the above criteria for either major bleeding or CRNMB.

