### Statistical analysis

#### Sample size calculation

The most important safety outcome of this prospective observational study is major bleeding. In the literature the mean prevalence of major bleeding in neonates with antithrombotic agents is about 10%. With this national guideline we expect the effect on the outcome of major bleeding in all neonates, to decline from 10 to 5%. Given that we have 150 neonates, the 95% CI will be about 2.5 to 9.9%, which means that we have a large probability of a significant difference with the literature. The formula for the CI is based on the binomial distribution for independent cases.

Baseline data will be analysed by descriptive statistics. Data will be presented as mean and standard deviations or medians and ranges depending on their distribution. The proportion of patients who developed the primary and secondary outcomes will be shown. Continuous variables will be analysed using Student’s *t* test or Mann-Whitney test. Categorical data will be analysed using chi-square test or Fisher exact test. The proportion of patients with various risk factors for CVC-thrombosis will be calculated. The significance level is set at *p* < 0.05. Data will be analysed using PASW Statistics (SPSS) 20.0.

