## Discussion

Advances in medical and surgical management has improved survival of sick (preterm) neonates, but has caused an increased incidence of thrombo-embolic complications. Lack of prospective clinical trials of antithrombotic treatment in (preterm) neonates leads to extrapolation of results of adult management studies to children. However, extrapolation of adult results to (preterm) neonates is difficult due to differences between neonatal and adult hemostasis and the presence of severe underlying medical conditions increasing the risk of bleeding complications in these vulnerable infants [26].

Furthermore, natural history of neonatal thrombosis seems to differ from that of adult thrombosis, as about 50% of neonatal thrombi appears to vanish without anticoagulant therapy. Determination of the natural history of neonatal thrombosis and identification of these “non-risky” thrombi is important to safely withhold anticoagulation in future patients.

As result of the national guideline, antithrombotic treatment of neonatal CVC-thrombosis has become identical on all NICUs in the Netherlands. Prospective collection of the neonates treated according to the protocol will enable evaluation of the used management strategy and generate data that can be used in follow-up treatment studies. For example, the NEOCLOT study allows investigating the natural history of specific neonatal catheter-related clots. In the current guideline “non-risky” thrombi were defined as non-obstructive thrombi in veins and thrombi filling less than 50% of the right atrium. Wait and see policy is applied to these thrombi. Results of the NEOCLOT study will show whether it will be safe to withhold anticoagulation in neonates with these thrombi.

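### The planned fall in major bleeding from 10% to 5% is set on all 150 infants, although both the outcome and the 10% benchmark concern treated infants only

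*Protocol article*

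**What the plan says.** Four parts of the protocol article bear on this.

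- **Outcome** (Outcomes of primary aims): "The primary safety outcome is the incidence of major bleedings during thrombolytic and anticoagulant therapy".
- **Benchmark** (Sample size calculation): "In the literature the mean prevalence of major bleeding in neonates with antithrombotic agents is about 10" percent.
- **Expectation and precision** (same section): "we expect the effect on the outcome of major bleeding in all neonates, to decline from 10 to 5" percent, followed by "Given that we have 150 neonates, the 95% CI will be about 2.5 to 9.9" percent. From this interval the article infers that a significant difference from the literature is likely.
- **Who the 150 are**: the abstract describes the cohort as "including 150 preterm and term infants (0-6 months) admitted to one of the 10 NICUs, developing CVC-thrombosis", and the inclusion criterion reads "All preterm and term infants (0-6 months) admitted on one of the NICUs with CVC-thrombosis will be included". Neither depends on treatment.

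The guideline under study leaves a defined group without antithrombotic treatment at the outset. In veins, "For non-obstructive CVC-thrombosis, a “wait and see” policy is recommended". In the right atrium, the same policy applies to thrombi taking up less than half of the atrium without an indication for thrombolysis. The Discussion calls both groups non-risky and confirms: "Wait and see policy is applied to these thrombi". In both locations, anticoagulation starts if the thrombus extends.

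**The concern.** The comparison joins three quantities that do not share a population. The event can occur only while an infant is on therapy, and the 10% reference comes from infants on therapy. The expected 5% and its interval, however, refer to every infant with catheter-related thrombosis. Each never-treated infant adds one to the denominator and, by definition, nothing to the numerator.

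This is the primary safety outcome of a study meant to evaluate a national guideline, and the sample size paragraph is the only place that names a reference value and an inference for it. The mismatch pushes the result towards apparent safety: a rate below 10% could be read as safer antithrombotic therapy when it reflects only how many infants were not treated.

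**Working it through.** **Inputs from the article:** cohort 150; benchmark 10%; expected rate 5%; two-sided 95% binomial interval (sidedness is not stated, so two-sided is taken). **Assumed:** the share *f* of infants ever treated, varied from 100% down to 50%, because the article gives no figure.

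**1. The article's own interval.** 5% of 150 is 7.5 events. The Wilson interval is 2.50 to 9.75%, Agresti-Coull 2.33 to 9.91%, and exact (Clopper-Pearson) 2.11 to 9.81%. The stated interval of about 2.5 to 9.9% is closely matched with *n* = 150. At 120, the exact upper limit is already 10.57% and the Wilson limit 10.48%. The planning denominator is therefore the whole cohort.

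**2. Event count needed.** The exact upper limit is 9.38% for 7/150 and 10.24% for 8/150. Excluding 10% therefore requires at most 7 events.

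**3. Dilution when therapy is no safer.** Take a true risk of 10% in treated infants and zero countable events in never-treated infants.

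- All-infant rate = 0.10 × *f*
- Chance of an upper limit below 10% = P(X ≤ 7), with X ~ Binomial(150, 0.10 × *f*)
- Treated risk implied by an all-infant rate of 5% = 0.05 / *f*

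| Share treated *f* (assumed) | All-infant rate | Chance that upper limit < 10% | Treated risk implied by 5% overall |
|---|---|---|---|
| 100% | 10% | 1.4% | 5.0% |
| 80% | 8% | 8% | 6.3% |
| 70% | 7% | 17% | 7.1% |
| 60% | 6% | 32% | 8.3% |
| 50% | 5% | 52% | 10.0% |

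With half the infants treated, the whole projected fall from 10 to 5% appears without any change in the risk on therapy.

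**4. Matching the denominator to the benchmark.** Take a true risk of 5% in treated infants. The exact interval is computed at 5% of *n*, and the last column is the binomial chance of seeing no more than the maximum event count.

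| Treated infants | Exact 95% CI at 5% | Most events that exclude 10% | Chance of excluding 10% |
|---|---|---|---|
| 150 | 2.1 to 9.8% | 7 | 52% |
| 120 | 1.9 to 10.6% | 5 | 44% |
| 105 | 1.7 to 11.1% | 4 | 39% |
| 90 | 1.5 to 11.7% | 3 | 34% |
| 75 | 1.3 to 12.6% | 2 | 27% |

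From 120 treated downwards, the interval at the expected rate includes 10%.

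**The case against.** The strongest counter-argument is that the study evaluates a management strategy, not a drug. If the guideline treats fewer infants and fewer bleed as a result, a lower rate among all infants is a genuine effect. In the scenarios above, the all-infant rate really is 5 to 8%. This stands, so the fall cannot simply be called spurious. It does not rescue the comparison, though: a strategy-level claim needs bleeding counted in every infant and a benchmark drawn from all infants with such thrombosis. The outcome definition excludes the first, and the 10% figure is not the second.

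Several stronger readings are tempting but unsupported:

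- *That the final analysis will divide by 150.* The article fixes this denominator only in the planning paragraph. For the analysis, it says only that proportions of patients with the outcomes will be shown, and it sets out no formal test against 10%. The 7-event threshold is the consequence of reading the interval against 10%, not a rule in the article.
- *That no wait-and-see infant can have the event.* Those whose thrombus extends start anticoagulation and become at risk. Only the never-treated dilute the rate.
- *That bleeding in untreated infants goes unrecorded.* The Data collection section lists bleeding among complications of therapy, but that is a condensed list and the case report form is not shown.
- *That the denominator explains all of the weak precision.* With all 150 treated and a true 5%, the chance of excluding 10% is only about 52%. At 120 treated, it drops from 52 to 44%, so most of the shortfall there comes from the sample size itself.

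**Conclusion.** The planned comparison is wrong as written. The mismatch between outcome, benchmark and denominator follows from the article's own text, and its direction is certain as soon as any infant is never treated. Its size rests on the treated share, which the article does not give. Over an assumed range of 80 to 50% treated, with no improvement on therapy, the chance of an upper limit below 10% rises from 1.4% to between 8 and 52%.

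The conclusion applies to the planning comparison and to any later reading of the all-infant rate against 10%. It does not establish that the final analysis will make this error, nor does it deny that treating fewer infants may be a benefit. The claim that a significant difference is likely is not supported in either case: the chance is about 52% with 150 treated infants and 27 to 44% with 75 to 120.

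**What to change.** 1. For the comparison with the 10% literature rate, define the proportion as treated infants with a major bleed during therapy, divided by infants who received any thrombolytic or therapeutic anticoagulant. The denominator should not be limited to the preferred agents, because the outcome covers all such therapy.
2. State the expected number treated. Restate the confidence interval and the probability claim for that number, using the second table in the working as a guide.
3. Report major bleeding in never-treated infants separately, over the same window from diagnosis. State that the all-infant rate will not be compared with the treated-only 10%. A strategy-level claim would need bleeding counted in all infants and an all-infant benchmark.
4. Describe the treated-only comparison as open to confounding by selection and treatment mix. The guideline directs therapy to obstructive, extending or high-risk thrombi. The Background also reports different bleeding rates by agent: 4% major bleeding (9 of 217) on enoxaparin, but 10% intraventricular bleeding alone on r-tPA.

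The cost is a wider stated interval, a weaker precision claim and a small amount of extra reporting. Enrolment and clinical management do not change.

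### The sample-size paragraph promises a large chance of a significant difference from the literature, but its own assumptions give about 52%

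*Protocol article*

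**What the plan says.** Under Statistical analysis, the sample size calculation of the protocol article names major bleeding as the most important safety outcome. It puts the literature rate at about 10% and expects that, under the guideline, "we expect the effect on the outcome of major bleeding in all neonates, to decline from 10 to 5" per cent. The number of infants enters as "Given that we have 150 neonates". From these inputs it states that "the 95% CI will be about 2.5 to 9.9%, which means that we have a large probability of a significant difference with the literature". On method it adds: "The formula for the CI is based on the binomial distribution for independent cases". The significance level is 0.05. Sidedness is not stated, and no power figure is given.

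**The concern.** The interval is evaluated at the expected rate, 5% of 150, and its upper limit of 9.9% lies just under the reference of 10%. The plan treats this as showing that significance is likely. But the observed count will fall above or below its expectation about equally often. A slightly higher count than expected moves the upper limit past 10%. An interval that barely excludes the reference at the expected value therefore points to a probability near one half.

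This comparison is the only rationale given for 150 infants, and it concerns the primary safety outcome. A reader who trusts the statement could take 8 or more major bleedings as evidence that the guideline did not lower the bleeding rate, although such a result is nearly as likely as not even if the rate has been halved.

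**Working it through.** **Inputs**, all from the sample size calculation: reference rate p0 = 0.10, treated as fixed; expected rate p1 = 0.05; n = 150, all neonates; 95% CI, which corresponds to a two-sided level of 0.05.

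**1. Reproducing the stated interval.** The expected count is 150 × 0.05 = 7.5. The logit interval is logit(p) ± 1.96 / √(n p (1 − p)):
- logit(0.05) = ln(0.05/0.95) = −2.944
- standard error = 1/√(150 × 0.05 × 0.95) = 1/√7.125 = 0.3746, and 1.96 × 0.3746 = 0.734
- limits on the logit scale −3.679 and −2.210, which back-transform to 2.46% and 9.88%

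This matches the stated 2.5 to 9.9%. Other methods at 7.5 events give:

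| Method | 95% CI |
|---|---|
| Wilson | 2.50 to 9.75% |
| Agresti-Coull | 2.33 to 9.91% |
| Clopper-Pearson (exact) | 2.11 to 9.81% |
| Wald | 1.51 to 8.49% (does not match) |

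**2. Largest count that excludes 10%.** Upper 95% limits with n = 150:

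| Events | Exact | Wilson | Agresti-Coull | Logit | Exact two-sided p against 10% |
|---|---|---|---|---|---|
| 7 | 9.38% | 9.32% | 9.49% | 9.46% | 0.028 |
| 8 | 10.24% | 10.17% | 10.33% | 10.30% | 0.056 |

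By all four intervals, significance requires 7 events or fewer.

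**3. Probability of that result.** P(X ≤ 7 | n = 150, p = 0.05) = Σ C(150, x) 0.05^x 0.95^(150−x) for x = 0 to 7 = **0.523**. The probability of missing the assumed halving is 1 − 0.523 = 0.477. The attained lower-tail error at p = 0.10 is 0.014.

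**4. Other readings.**

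| Reading | Probability of significance |
|---|---|
| Normal approximation, null variance, two-sided | 54% (47% with continuity correction) |
| Arcsine approximation, two-sided | 65% |
| Jeffreys interval (8 or fewer events) | 66% |
| One-sided exact test at 0.05 (8 or fewer events) | 66% |
| Wald interval (9 or fewer events), exact summation | 78% |

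The normal-approximation formula for the Wald case gives 80%, but the Wald interval is not the one the plan quotes.

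**5. Scale.** With the exact two-sided criterion, power first reaches 80% at n = 231, dips below again because counts are discrete, and stays at or above 80% from n = 255.

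**6. If the 10% is itself an estimate.** The sample size calculation gives no source or sample size for the 10%, so this step rests on an assumption. A two-sample normal approximation, with 150 infants at 5% and a reference group at 10%, gives 34% for a reference of 98 infants, 41% for 217, 44% for 315 and 50% for 1000.

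**The case against.** The strongest reply is that nothing has been miscalculated. The interval reproduces, evaluating precision at the expected rate is ordinary planning practice even though 7.5 events cannot occur, and "large" is a qualitative word with no power figure attached. The study is an observational cohort, the stated reporting of outcomes is mainly descriptive, and no success criterion or treatment decision depends on the comparison. The number 150 reads as given rather than derived. Sidedness is unstated, and because the expected change is a decline, a one-sided test could be meant.

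Much of this is fair. The interval is right; the fault is only in the inference drawn from it. The section also lists other tests, so this comparison is not its only inferential content. Any figure for uncertainty in the 10% is an assumption: the two reviews described in the Background (217 and 98 infants) are not cited as its source. Which interval to use for the primary safety analysis is a choice among valid methods.

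None of this rescues the claim. A one-sided test or the Jeffreys interval raises the probability only to 66%, and the Wald result belongs to an interval the plan did not use. A purely precision-based rationale would have been acceptable for an observational cohort, but the paragraph goes further and presents probable significance as following from the interval.

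**Conclusion.** The concern holds. Under the plan's own inputs, the probability that the 95% CI excludes 10% is about 52%, which cannot be called large. The figure assumes a true rate of exactly 5%, a fixed reference of 10%, a two-sided 5% level, and all 150 neonates in the denominator. The paragraph supports each of these. It is sensitive to the true rate: P(X ≤ 7) is 75% at a true rate of 4% and 32% at 6%. Allowing for sampling error in the literature rate would lower it, to between 34% and 50% for the assumed reference sizes shown.

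**What to change.** Delete the statement that significance is likely. Replace it with one of the following:

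- **State the probability.** For example: with 150 infants and a true rate of 5%, the exact 95% CI excludes 10% only if at most 7 major bleedings occur, which has probability about 52%.
- **Justify 150 by precision (preferable).** Give the expected interval, for example exact 95% CI 1.9 to 9.4% for 7 events and 2.3 to 10.2% for 8, and make no claim about significance.

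In either case, name the interval method and say that the 10% is treated as a fixed reference. Making the exact binomial interval the primary safety analysis would keep the analysis in line with this rationale, but it is optional.

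The cost is one reworded paragraph. The stated property becomes less favourable; sample size, conduct and data collection do not change.

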## Discussion

Advances in medical and surgical management has improved survival of sick (preterm) neonates, but has caused an increased incidence of thrombo-embolic complications. Lack of prospective clinical trials of antithrombotic treatment in (preterm) neonates leads to extrapolation of results of adult management studies to children. However, extrapolation of adult results to (preterm) neonates is difficult due to differences between neonatal and adult hemostasis and the presence of severe underlying medical conditions increasing the risk of bleeding complications in these vulnerable infants [26].

Furthermore, natural history of neonatal thrombosis seems to differ from that of adult thrombosis, as about 50% of neonatal thrombi appears to vanish without anticoagulant therapy. Determination of the natural history of neonatal thrombosis and identification of these “non-risky” thrombi is important to safely withhold anticoagulation in future patients.

As result of the national guideline, antithrombotic treatment of neonatal CVC-thrombosis has become identical on all NICUs in the Netherlands. Prospective collection of the neonates treated according to the protocol will enable evaluation of the used management strategy and generate data that can be used in follow-up treatment studies. For example, the NEOCLOT study allows investigating the natural history of specific neonatal catheter-related clots. In the current guideline “non-risky” thrombi were defined as non-obstructive thrombi in veins and thrombi filling less than 50% of the right atrium. Wait and see policy is applied to these thrombi. Results of the NEOCLOT study will show whether it will be safe to withhold anticoagulation in neonates with these thrombi.

